**Expected impact:**

It is hypothesized that WFPBDs will mitigate progression and severity of PNP and potentially reduce the adverse events related to standard corticosteroid treatment of leprosy reactions, thereby reducing disease severity. By examining the effects of WFPBDs on PNP in leprosy, we hope to illuminate data that will lead to the enhanced therapeutic management of this neglected tropical disease.

## 1. Introduction

Leprosy continues to affect nearly 200,000 individuals globally, despite being eliminated as a public health concern by the World Health Organization in 2000 (1). Causative agents, *Mycobacterium leprae* and *Mycobacterium lepromatosis*, prevail in low-middle income countries where many barriers to treatment adherence and effective prevention of neuropathic sequelae continue to challenge the clinical management of leprosy (1, 2). Patients experience hypopigmented and inflammatory cutaneous lesions, disabling sensory and motor neuropathies, and debilitating neuropathic pain, often leading to stigma and social ostracization (2–6). Despite the development of effective therapeutics via multidrug therapy (MDT), nerve release surgery, and other immunosuppressives decades ago, treatment of the associated neuropathic pain continues to remain largely ineffective. Standard pharmacological treatment of PNP using antidepressants, anticonvulsants, and opioids, results in a less than 30% reduction of pain (1, 7). Additionally, a significant side effect profile including anticholinergic effects, dizziness, confusion, hypertension, and weight fluctuation, contribute to poor adherence to PNP treatment overall (8). Given these extensive barriers, patients with leprosy sequelae, including PNP, continue to experience a reduced quality of life even with adequate access to gold standard therapeutics (6, 9, 10). In the absence of effective pharmaceuticals, alternative interventions must be explored to bolster patients’ control of leprosy sequelae and the associated morbidity.

Lifestyle interventions have recently emerged as accessible and cost-effective strategies to reduce the burden and severity of neuropathic pain in diabetes. Strategies seeking to improve physiological and metabolic wellness, including those that reduce inflammation and enhance immune responsiveness to neurotoxic factors may influence underlying neuropathic etiologies. Nutrient supplementation has been instrumental in reducing host oxidative stress, strengthening the immune system, and mitigating potential adverse events in both leprosy and diabetes (11–15). Specifically, oral vitamin E and zinc supplementation may confer antioxidant effects, reducing daily analgesic requirements, and decreasing the incidence of leprosy symptoms overall (14, 16, 17). Likewise, studies assessing the use of oral vitamin D3 and omega-3 supplementation in diabetes have shown statistically significant improvements on subjective tests of neuropathy and pain, as well as objective tests of nerve health (11–15). Dietary interventions have also been specifically shown to reduce overall symptomology and improve the quality of life of individuals suffering from PNP due to diabetes (18–22). Many leprosy patients will develop impaired glucose tolerance due to genetic and lifestyle factors alone, and also due to the reliance on corticosteroids for control of inflammatory leprosy reactions (which can occur before, during, and after effective MDT). As patients experiencing leprosy often endure a biochemically induced diabetes, similar rationale may be applied. Prior to a final diagnosis of leprosy, patients are statistically significantly more likely to have diabetes (up to 14.2%) or pre-diabetes (up to 50%), when compared to healthy controls. Likewise, up to 65% of patients require corticosteroid treatment following reactions, resulting in steroid-induced hyperglycemia in up to 47% of individuals who were previously glucose tolerant (23–28). Additionally, given the high population prevalence of diabetes, lifestyle and genetic factors may predispose those with leprosy to diabetic neuropathy independent of corticosteroid use.

A WFPBD emphasizing vegetables, fruits, grains, and legumes, while omitting animal products, and limiting saturated fat intake has recently been shown to reduce diabetes related PNP severity and symptomology (19, 21, 22, 29, 30). In a cohort study assessing a WFPBD in 21 participants with type 2 diabetes, a statistically significant reduction of both serum triglycerides and total cholesterol, alongside a noticeable decrease in pain, weight, and insulin requirements was reported (22). Likewise, data from over 110 observational and clinical trials suggest that dietary patterns similar to a WFPBD are associated with a decreased presence of diabetes and significant improvements in biochemical profiles, including total LDL, and therapeutic requirements, for insulin in particular (21). Finally, a comprehensive randomized control trial seeking to address neuropathic pain management in 34 participants with neuropathy due to diabetes corroborates previous findings. Using both subjective questionnaire and objective quantitative sensory testing (QST), and electrophysiology, a significant decline in weight, body mass index (BMI), and glycemia was observed alongside a statistically significant improvement in neuropathic pain (19). Overall, WFPBDs have proven to be effective in the management of neuropathy due to diabetes, limiting endoneural ischemia, and providing sufficient glycemic control and lipid management, which when uncontrolled seem to exacerbate neuropathic pain. As a result, this phenomenon may translate to the management of PNP in leprosy, where diabetes comorbidity is common, and research has shown that diet and lifestyle interventions may be sufficient to control such steroid-induced hyperglycemia (23–28, 30–32). A WFPBD may also provide enhanced nutritional and antioxidant intake, conferring neuro-protective effects against leprosy alone while patients are actively undergoing antimicrobial MDT.

Major dietician groups suggest that a WFPBD is efficacious and superior in most, if not all populations. Dieticians of Canada, the British Dietetic Association, and the American Academy of Nutrition and Dietetics promote WFPBDs, suggesting improvements in weight, cholesterol, and risk of cardiovascular disease and type 2 diabetes (33–35). These groups also endorse that a WFPBD meets or exceeds recommended lipid, vitamin, mineral, fiber, protein, and amino acid requirements, when sufficient caloric intake is achieved (33–35). The wholegrains, nuts, seeds, beans, and fruits and vegetables readily supplied by a WFPBD can maximize intake of thiamine, pyridoxine, cobalamin, omega-3, zinc, and vitamins A, C, and E which are crucial to neurotransmitter and myelin synthesis, action potential propagation, and neuroprotection via capturing free radicals, and reducing oxidative stress (36–39).

We hypothesize that a WFPBD will have a multipronged beneficial effect, providing sufficient nutrient intake, neuro-protective benefits, and glycemic control to enhance host control of leprosy sequelae. A comprehensive prospective, randomized, controlled, single-blind, multicentre trial examining the efficacy, safety, and tolerability of a whole food plant-based diet on PNP in leprosy will inform any association between nutritional interventions and disease severity at the population level. Through reliable and validated techniques, such as comprehensive questionnaires and objective QST, a robust data set and analysis is expected to be generated. Overall, it is hypothesized that WFPBDs will mitigate progression of PNP as well as adverse events related to standard corticosteroid treatment of reactions, resulting in decreased neuropathic pain severity. By evaluating our current knowledge regarding the effects of WFPBDs on neuropathic pain in leprosy, we hope to illuminate data that will lead to enhanced therapeutic management and control of the impact of this neglected tropical disease.

## 2. Methods and analysis

### 2.1. Study design

This is a prospective, randomized, controlled, single-blind, multicentre trial examining the efficacy, safety, and tolerability of a WFPBD versus standard diet within a population living with PNP due to leprosy. An analytic framework capturing the target population, intervention, comparator, intermediate and ultimate outcomes to be assessed, as well as the impacts and considerations underpinning such a trial is presented in Figure 1.

**Figure 1 fig1:**
[figure not shown]
Analytic framework. BMI, body mass index; BMR, basal metabolic rate; BP, blood pressure; CAD, coronary artery disease; DALY, disability-adjusted life year; DM2, Type 2 diabetes mellitus; HR, heart rate; HTN, hypertension; LFTs, liver function tests; MCV, mean corpuscular volume; WFPBD, whole foods plant-based diet.

### 2.2. Study objectives and hypothesis

The overall objective of this study is to demonstrate the effect of a dietary lifestyle intervention, specifically a WFPBD, on neuropathic pain variables in leprosy. It is hypothesized that patients may demonstrate a statistically significant improvement in sensory and motor neuropathy, as well as pain, on comprehensive questionnaires and objective QST and muscle testing both within and between groups at study end. Secondary objectives include contextualizing the significance of diet in the treatment of chronic leprosy sequelae by demonstrating high tolerability and a limited side effect profile alongside aforementioned improvements in neuropathic pain. It is hypothesized that a WFPBD has the potential to serve as a low-risk, low-cost, low-tech intervention for chronic neuropathic pain, improving function and reducing overall morbidity of leprosy.

### 2.3. Inclusion and exclusion criteria

Participants will be enrolled at the Tropical Disease Unit (TDU) in Toronto, Ontario, Canada, and one or more partner tropical medicine institutes, and will include patients experiencing active, or treated “cured” leprosy, as well as any degree of PNP. Inclusion into the trial requires: (1) clinically compatible leprosy based on the presence of thickened peripheral nerves (on physical exam, as well as ultrasound), and hypo- or anesthetic skin lesions; and/or (2) laboratory confirmed leprosy via positive slit skin smears and/or consistent histopathology and/or the presence of acid-fast bacilli on histopathology; and/or (3) a clinically compatible presence of neuropathy on physical exam including but not limited to glove and stocking paresthesia, abnormal touch perception sensations, and subjective pain (40–42) (Table 1). Sensory perception will be evaluated using 0.2–0.6 g Semmes-Weinstein monofilament, and the presence of 2/3 insensate sites will be considered “abnormal” (43). The use of objective QST as a standalone test for inclusion will be dependent on enrolment frequency to better preserve trial specificity. In the event of inadequate enrolment, a negative QST will not exclude patients from the trial to ensure adequate sensitivity, and vice versa. QST unreliably detects small fiber neuropathy, potentially representing a large portion of the target population (44, 45). Therefore, it is unlikely that it will remain a standalone inclusion criterion, however, will still be collected for downstream analysis. Finally, prospective participants who are pregnant, <18 years of age, already following a WFPBD (including vegetarian and vegan diets), and those experiencing neuropathy due to other significant causes alone, will be excluded (Table 1). Leprosy patients who fulfill inclusion criteria experiencing a biochemical diabetes due to corticosteroid therapy will remain eligible for inclusion and will be considered in downstream analysis (23–28). No restriction on language will be implemented as translation services will be made available across study centres.

**Table 1 tab1:** Inclusion and exclusion criteria.

Inclusion	Exclusion
Presence of leprosy	Pregnancy
Clinical compatibility:	<18 years old
Thickened peripheral nerve	Already following a whole food plant-based diet
Presence of skin lesions	
Laboratory confirmation:	Experiencing neuropathy due to other significant underlying causes^†^
Positive slit skin smears	
Acid-fast bacilli on histopathology	No restriction on language as translation services will be provided
Presence of neuropathy	
Clinical compatibility on physical exam*:	
Glove and stocking paresthesia	
Abnormal touch perception sensations	
Subjective presence of pain	

*Including but not limited to; ^†^Excluding biochemically induced diabetes.

### 2.4. Dietary intervention

#### 2.4.1. Protocol diet and supporting evidence

The David Jenkins Portfolio Diet was originally designed to lower blood lipid levels in patients with hypercholesterolemia by emphasizing vegetables, fruits, grains, and legumes, while omitting animal products, and limiting saturated fat intake (46, 47). Specifically, the diet focuses on plant sterols (1 g/1000 kcals) as enriched margarine, soy and vegetable proteins (23 g/1000 kcals) as soy milk, meat alternatives, nuts, beans, chickpeas, and lentils, viscous fibers (9 g/1000 kcal) in the form of oats, barley, and psyllium, and low-calorie fruits and vegetables (46, 47) (Table 2). Following a comprehensive interventional trial in which 13 participants received the portfolio diet, a statistically significant reduction of LDL cholesterol, and coronary artery disease was observed (*p* < 0.001) alongside high compliance (93%) and acceptability (*p* = 0.042) (47). Similarly, in recent literature interventional trials have emerged assessing the efficacy of a WFPBD, like that of the portfolio diet, for neuropathic pain in individuals with diabetes. Specifically, in a trial assessing a low-fat plant-based diet, omitting animal products, and limiting fat intake to 20–30 g/day in 34 patients, a statistically significant reduction of pain on subjective neuropathy questionnaires and neuropathy on objective electrophysiology was observed (*p* < 0.05) (19). WFPBDs have been shown to provide sufficient glycemic control and lipid management which, when left unchecked, can exacerbate diabetes-related neuropathy. Given the absence of literature concerning the intersection of dietary lifestyle interventions and neuropathic pain of leprosy, it is hypothesized that a WFPBD will have similar physiological and neuro-protective benefits in a cohort of patients with leprosy and its neuropathic sequelae, in whom diabetes comorbidity is frequent.

**Table 2 tab2:** Example portfolio diet for one day.

Breakfast		Lunch		Dinner		Snacks	
35 g	Oatbran	65 g	Vegetable chili	295 g	Vegetable curry	14 g	Almond × 2
150 g	Orange	67 g	High fiber bread	85 g	Soy burger	250 g	Soymilk × 2
7 g	Metamucil	17 g	Margarine	80 g	Beans	7 g	Metamucil × 2
33 g	High fiber bread	62 g	Soy deli slices	35 g	Barleys	175 g	Soy yogurt
8 g	Margarine	80 g	Tomato	100 g	Okra	10 g	Jam
18 g	Jam	150 g	Orange	200 g	Eggplant		
250 g	Soy milk			200 g	Cauliflower		
				80 g	Onions		
				60 g	Red pepper		

Adapted from “A dietary portfolio approach to cholesterol reduction: combined effects of plant sterols, vegetable proteins, and viscous fibers in hypercholesterolemia.” by Jenkins et al. (47).

#### 2.4.2. Lifestyle counseling

Participants in the intervention group will be instructed to follow a WFPBD for 24 weeks. The study duration was chosen as a conservative estimate of comparable lifestyle-based interventional trials that demonstrated statistically significant improvements in diabetes-related neuropathy outcomes (18, 19). The diet will emphasize vegetables, fruits, whole-grains, nuts, and legumes, while omitting animal products, and limiting fat intake (Table 2). Selection of specific plant-based components may differ across study sites in concordance with local culinary preferences and cultural practices related to food. By tailoring the diet to the unique cultural diaspora affected by leprosy, many of which already endorse plant-based components, we seek to enhance adherence and acceptability to the diet overall. Likewise, current economic projections suggest that diets seeking to reduce animal products are more affordable than current standard diets across all socioeconomic levels – particularly due to inclusion of global staples such as tubers, beans, legumes, and rice – further enhancing accessibility (48–50). Participants will receive weekly support and guidance via 1 h counseling sessions with registered dieticians or the equivalent at each participating site. Sessions will be designed to disseminate comprehensive guidelines for following the WFPBD including culturally acceptable recipes and addressing concerns or knowledge gaps regarding the intervention. Participants in both the intervention group, and control group will be instructed to continue their respective leprosy therapeutics as prescribed throughout the duration of the study. Finally, dietary adherence will be measured via monthly random 24 h dietary recalls, and participants are free to withdraw at any point during the trial if they no longer wish to participate.

### 2.5. Methodology

#### 2.5.1. Collaboration

Clinical manifestations of leprosy are highly variable, hinging on several geographic, cultural, and genetic underpinnings (2). As such, to maximize the impact of trial outputs, we seek to address the global experience of leprosy through collaboration between the TDU in Toronto, Ontario, Canada, and one or more partner centres for excellence in the care of Hansen’s disease patients abroad. Given migration patterns, selected study centres will account for endemic source countries and regions including the Philippines, the Indian sub-Continent, Southeast Asia, and South America, providing for a more representative data set (2, 51). Trial documents including patient informed consent will be prepared in multiple languages to harmonize procedures across study sites. Likewise, site leads at each respective centre will be responsible for coordinating recruitment, as well as data collection. Oversight will be maintained by a centralized lead at the TDU, who will be responsible for disseminating the randomization protocol, and ensuring overall procedural adherence across sites.

#### 2.5.2. Consent, randomization, and blinding

Patients with a history of leprosy will be pre-screened for inclusion via clinical records prior to routine follow up. Study personnel will approach eligible patients experiencing active or treated (“cured”) leprosy, as well as subjective neuropathic pain at participating tropical disease institutions. Eligible participants will receive a comprehensive in-person review of the trial protocol, including data collection requirements, and will be given the patient consent form. Patients will voluntarily confirm willingness to participate and will be free to withdraw at any point. Upon consent to enrolment, participants will be randomized to either the WFPBD intervention group, or standard of care control group. To ensure equal distribution and matching between study groups, randomization will be carried out using a stratified block method (52). Participants will be assigned to strata primarily by study site, followed by sex (male/female), and lastly age-band (18–65, >65) (Figure 2). Random sequence generation will be carried out using a computer-generated allocation sequence. Study investigators, physicians, and participants will not be blinded to group allocation due to the transparent nature of the dietary intervention and counseling. However, primary end points will be collected by independent study personnel, blinded to group allocation, allowing for a single-blinded protocol.

**Figure 2 fig2:**
[figure not shown]
Stratified, block, randomization protocol. Adapted from: “Randomization in clinical studies.” by Lim and In (52). TDU, Tropical Disease Unit.

### 2.6. Statistical analysis

#### 2.6.1. Sample size calculation

This is a novel RCT addressing the implications of a WFPBD on neuropathic outcomes in individuals with leprosy. This relationship has not been directly assessed in the current body of literature, however similar research questions have been assessed in individuals with diabetes mellitus. As such, the sample size calculation herein will utilize this literature as a proxy. The efficacy of a WFPBD diet on neuropathy in a diabetes cohort has been reported via the Michigan Neuropathy Screening Instrument (MNSI), including both subjective (questionnaire) and objective (physical assessment) measures. The sample size calculation was based on the MNSI questionnaire measurement as explicit details pertaining to the MNSI physical assessment were not provided. Specifically, both the type of QST utilized (vibration, perception, both, etc.) and the location the test was carried out (lesion, glove, stocking, etc.) were not mentioned. Therefore, the MNSI questionnaire was preferentially chosen as a proxy. Participants receiving the intervention reported a final mean MNSI questionnaire of 5.3 ± 2.5 compared to 7.1 ± 2.8 in the control group at study end (19). Using an opensource sample size calculator with two independent study groups, continuous endpoints, an alpha of 0.5 and 80% power, a final sample size of approximately 60 participants was ascertained (53, 54). This is a conservative estimate as source literature demonstrated a statistically significant effect on outcomes with a relatively low population of 34 individuals (19). Assuming high acceptability and a 14% withdrawal and/or loss to follow-up rate based on previous literature, a final sample size of ~70 individuals, 35 per group, will be needed to adequately power this trial (19, 47, 55, 56).

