#### 2.6.2. Continuous and categorical variables

Descriptive statistics including reported means ± standard deviation for continuous variables [questionnaires including MNSI-physical assessment, Neuropathy Total Symptom Score (NTSS), modified Medical Research Council Scale (mMRCS), Neuropathic Pain Symptom Inventory (NPSI), McGill Pain Questionnaire (MPQ), Pittsburgh Sleep Quality Index (PSQI), and International Physical Activity Questionnaire (IPAQ) summative scores, visual analog scale (VAS), anthropometrics, diabetes duration, hemoglobin A1c, and serum micronutrient levels] and proportions for categorical variables [number of adverse events, dietary adherence, insulin use, leprosy clinical status (according to the WHO and Ridley Jopling classification systems), frequency and prevalence of inflammatory leprosy reactions, corticosteroid use] will be reported by each study group (57). Between- and within-group comparisons will also be made for continuous variables using the Student’s *t*-test with reported *p*-values, and for categorical variables using the chi square or Fisher’s exact tests, reporting *p*-values with odds ratios and 95% confidence intervals. Statistics will also be reported for all time points including baseline, and end of study. Multivariate logistic regression adjusting for covariates [such as age, sex, PROGRESS+ factors (58, 59), level of physical activity, smoking status, alcohol consumption, comorbidities, diabetes status] and potential effect modifiers (such as change in weight over time, medication de-escalation over time) will be carried out to ascertain the impact of a WFPBD on PNP in leprosy patient sub-populations and under various conditions. All statistical analysis will be carried out using GraphPad Prism 8 (GraphPad, United States).

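### The printed alpha of 0.5 cannot give 60 participants, and with both quoted SDs at two-sided 0.05 the 60 evaluable give about 73% power, not 80%

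*Protocol article*

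**What the plan says.** All of the sample size reasoning is in section 2.6.1 of the protocol article. The effect comes from a trial of a plant-based diet in diabetic neuropathy, with a "final mean MNSI questionnaire of 5.3 ± 2.5 compared to 7.1 ± 2.8 in the control group" at study end. The calculation is described as one for "two independent study groups, continuous endpoints", and its settings and result are given as "an alpha of 0.5 and 80% power, a final sample size of approximately 60 participants was ascertained". The next sentence defends the result: "This is a conservative estimate as source literature demonstrated a statistically significant effect on outcomes with a relatively low population of 34 individuals". After an allowance of 14% for withdrawal and loss, the section concludes that "a final sample size of ~70 individuals, 35 per group, will be needed to adequately power this trial".

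Section 2.6.1 does not say whether the test is one- or two-sided, or which SD was entered. No other section gives a different alpha. Section 2.6.2 plans Student's t-tests for continuous outcomes and, for categorical outcomes, "reporting *p*-values with odds ratios and 95% confidence intervals".

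**The concern.** The section prints every main input (means, SDs, alpha, power) and the result, so it can be checked directly, and the result does not follow from the inputs. Two things are wrong. The alpha as printed is a 50% type I error rate. Once alpha is read in the usual way, the sample size is smaller than the quoted means and SDs require.

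This is the trial's only justification of its size. If the power is nearer 73% than 80%, a true effect of the assumed size is missed about 27% of the time instead of 20%. A reader of a null result would be relying on a claim of adequate, even conservative, power that the inputs do not support.

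**Working it through.** **Inputs (section 2.6.1 unless stated).** Difference 7.1 − 5.3 = 1.8. SDs 2.5 and 2.8. Power 80%. Equal arms (35 per group enrolled). Loss 14%. Test: Student's t-test (section 2.6.2). Alpha is printed as 0.5; 0.05 is my reading. Sidedness is not stated, so both are shown.

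**Formula (normal approximation).** n per arm = (z_alpha + z_power)² × (SD₁² + SD₂²) / difference².

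With both SDs: 2.5² + 2.8² = 6.25 + 7.84 = 14.09, and 1.8² = 3.24, so the ratio is 4.349. The pooled SD is √(14.09/2) = 2.654, and the standardised difference is 1.8/2.654 = 0.678.

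**Step 1. Try to reproduce 60 with the printed alpha.** Two-sided 0.5: (0.674 + 0.842)² × 4.349 = 2.299 × 4.349 = 10.0 per arm, or 20 in total. One-sided 0.5 gives 4 per arm, or 8 in total. At 30 per arm, two-sided 0.5 would give about 97.5% power. So 0.5 is not the value that produced 60.

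**Step 2. Two-sided 0.05, both SDs.** (1.960 + 0.842)² × 4.349 = 7.849 × 4.349 = 34.13, hence 35 per arm or 70 in total. The t-test needs 36 per arm or 72 in total.

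**Step 3. Search for an input that gives 60.** Total evaluable for 80% power, and t-test power at 30 per arm:

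| Alpha | SD used | n per arm before rounding (normal) | Total (normal / t-test) | Power at 30 per arm (t-test) |
|---|---|---|---|---|
| 0.05 two-sided | both | 34.1 | 70 / 72 | 73.3% |
| 0.05 two-sided | 2.5 only | 30.3 | 62 / 64 | 78.3% |
| 0.05 two-sided | 2.8 only | 38.0 | 76 / 78 | 68.7% |
| 0.05 one-sided | both | 26.9 | 54 / 56 | 82.9% |
| 0.05 one-sided | 2.8 only | 29.9 | 60 / 62 | 79.3% |

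A total near 60 appears in two rows: SD 2.5 alone with a two-sided test, and SD 2.8 alone with a one-sided test. Each leaves out one of the two SDs quoted, and the article states neither choice.

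**Step 4. Power of the planned trial.** For the t-test with 30 per arm, the noncentrality is 1.8 / (2.654 × √(2/30)) = 2.627 on 58 degrees of freedom. The two-sided 5% critical value is 2.002, and the power is 73.3%. The normal approximation gives 74.7%.

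**Step 5. Loss to follow-up.** 60/0.86 = 69.8, so 70 enrolled is correct given 60, and 70 × 0.86 = 60.2 are left. If all 70 were evaluable, power would be 79.9% (t-test). The enrolled number is therefore roughly what is needed before any loss. Keeping 80% after 14% loss would take 70/0.86 = 81.4 to 72/0.86 = 83.7, that is 82 to 84 enrolled.

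**The case against.** The best defence has three parts.

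First, 0.5 is plainly a slip for 0.05. The 95% intervals in section 2.6.2 point that way, and few readers would be misled. That is fair, but it is still the only alpha the article prints.

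Second, the total is given only as approximate, and a single common SD is an ordinary input for an equal-variance t-test. With SD 2.5 the normal formula gives 30.3 per arm, and power at 30 per arm is 78.3%, close to target. This stands as a plausible account of where 60 came from. It does not justify the figure: the smaller of two quoted SDs was then used without saying so, which is the optimistic choice.

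Third, the 73% depends on a two-sided test, which section 2.6.1 does not state. This stands. With one-sided 0.05 and both SDs, 60 evaluable would exceed the 80% target. Two-sided is the more natural reading, because the 95% intervals suggest it (although they are stated for odds ratios) and no section mentions a one-sided test.

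A reader might also go further and infer that the diabetes trial was not significant at all. If its 34 participants were split 17/17, the quoted final means and SDs give t = 1.98 and p = 0.057. The documents do not support that inference. They do not give that trial's arm sizes, or say whether final values or changes were tested. Section 2.6.1 refers only to outcomes in general, and section 2.4.1 attributes the significance to pain questionnaires and electrophysiology. The case against the word conservative does not need it.

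**Conclusion.** The point holds. The printed alpha, power and sample size cannot all be right. With alpha read as two-sided 0.05 and both quoted SDs used, the requirement is 10 to 12 evaluable participants above the stated 60, and power falls about 7 percentage points short of the stated 80%. The size of the shortfall rests on that reading of alpha, on the planned t-test, and on the quoted diabetes figures as a proxy, which the article openly acknowledges. It would be too strong to say that the trial is underpowered under every reading. What holds under every reading tried is that no stated set of inputs yields 60. The claim of a conservative estimate fails on the two-sided reading because 60 is below what the plan's own inputs require. The step from 60 to 70 for loss is correct.

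**What to change.** In section 2.6.1:

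1. Correct alpha to 0.05, and state whether the test is one- or two-sided and which SD was entered.
2. Restate that 70 enrolled and 60 evaluable give about 73% power for a two-sided t-test with SDs 2.5 and 2.8. If 80% is to be kept for that test, the total has to be recalculated instead (82 to 84 enrolled).
3. Delete the sentence that calls the estimate conservative. Do not put the p = 0.057 recalculation in its place, because it depends on details of the diabetes trial that the article does not give.
4. If power for a baseline-adjusted analysis is quoted, label it as resting on an assumed correlation between baseline and final score. With 60 evaluable it is about 77% at a correlation of 0.3, 80% at 0.4 and 85% at 0.5. The article gives no such correlation, and section 2.6.2 plans t-tests for these outcomes, so this cannot by itself restore the 80% claim.

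The cost is wording and one recalculation. Restating the power needs no extra participants but makes the stated power less favourable. Holding 80% for the t-test means enrolling 12 to 14 more.

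### The sample size is called conservative, but it uses one small diabetic trial's observed difference without margin and gives about 73% power, not 80%

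*Protocol article*

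**What the plan says.** Section 2.6.1 explains that the question has not been studied in leprosy and that diabetes literature serves as a proxy. The planning values are these: "Participants receiving the intervention reported a final mean MNSI questionnaire of 5.3 ± 2.5 compared to 7.1 ± 2.8 in the control group at study end". The calculation assumes two independent groups and a continuous endpoint, with "an alpha of 0.5 and 80% power", and arrives at about 60 participants. The next sentence defends that figure: "This is a conservative estimate as source literature demonstrated a statistically significant effect on outcomes with a relatively low population of 34 individuals". Allowing 14% loss, the section raises the number to about 70 (35 per group) and says this powers the trial adequately.

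Two other places bear on the point. The Introduction describes the source trial as addressing "neuropathic pain management in 34 participants with neuropathy due to diabetes". Section 2.3 says that enrolment here "will include patients experiencing active, or treated “cured” leprosy, as well as any degree of PNP". Diabetes is not required, although steroid-induced diabetes does not exclude a patient.

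**The concern.** A sample size is conservative when its inputs are cautious: an effect smaller than the one observed, an SD on the high side, or both. Here the effect is the source trial's whole observed difference. That a small trial reached significance on some outcomes does not show its observed difference to be a cautious value. The estimate is imprecise, and it comes from a cohort in which everyone had diabetic neuropathy.

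What is at stake is how the result will be read. If the trial finds no significant difference, a reader who trusts this paragraph will think a useful effect had been given a better than 80% chance of showing. On the paragraph's own figures the chance is below 80% even if the full diabetic effect carries over, and it falls quickly for smaller effects.

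**Working it through.** **Inputs** (section 2.6.1 unless noted)
- Means 7.1 (control) and 5.3 (intervention): difference 1.8.
- SDs 2.8 and 2.5. Equal-arm pooled SD = √((2.8² + 2.5²)/2) = √7.045 = 2.654. Standardised difference = 1.8/2.654 = 0.68.
- Power 80%; 14% loss; about 60 evaluable; about 70 enrolled.
- Student's t-test (section 2.6.2).
- Assumptions: alpha is 0.05, because the printed 0.5 would give only 18 to 24 participants in total two-sided. The test is two-sided; the article does not say.

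**Reproducing the plan's figure.** Per arm, n = 2(1.960 + 0.842)² SD²/1.8².

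| SD used | n per arm, unrounded | Total, rounded up |
|---|---|---|
| 2.5 | 30.3 | 62 |
| 2.654 | 34.1 | 70 |
| 2.8 | 38.0 | 76 |

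Two-sided, about 60 is approached only with the smaller SD. A one-sided 0.05 test with SD 2.8 also gives 60 (29.9 per arm). The loss allowance reproduces: 60/0.86 = 69.8, so 70.

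**Power at 30 per arm for 1.8 points** (noncentral t, two-sided 0.05)

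| SD | Power |
|---|---|
| 2.5 | 78% |
| 2.654 (both SDs) | 73% |
| 2.8 | 69% |

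The normal approximation gives 80%, 75% and 70%. With both SDs, all 35 per arm would have to be evaluable to reach 80% (79.9% by the t-test).

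**Detectable difference.** With 30 per arm and the pooled SD, 80% power requires 1.95 points, more than the 1.8 planned for.

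**Power at smaller differences** (30 per arm, pooled SD)

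| Difference | Power |
|---|---|
| 1.8 | 73% |
| 1.5 | 58% |
| 1.2 | 41% |
| 0.9 | 25% |

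**How firm is 1.8?** The article does not give the arm sizes of the 34. At 17 and 17:
- SE = √((2.5² + 2.8²)/17) = 0.910.
- t = 1.8/0.910 = 1.98 on 32 df, two-sided p = 0.057.
- 95% CI = 1.8 ± 2.037 × 0.910 = -0.05 to 3.65.

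Over all splits of 34, the smallest p from the printed values is 0.056, pooled or Welch. The inputs are rounded to one decimal. Means of 7.15 and 5.25 with the printed SDs give p = 0.045; with SDs of 2.75 and 2.45 as well, p = 0.041. Power for 1.8 points at 17 per arm is 48%.

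**The case against.** The strongest reply is that the protocol is open about its proxy: it says the question is untested in leprosy and explains the choice of the MNSI questionnaire. It also plans to adjust for diabetes status and to stratify by diabetes status and steroid use. That stands as disclosure of the source. It does not justify the word conservative, and stratifying does not restore power.

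A reader might infer from p = 0.057 that the source's MNSI result was not significant, so that the cited significance must belong to some other outcome. The documents do not support that. Rounding alone could bring p to about 0.04, and a normal approximation near equal arms gives about 0.048. The source may also have tested change from baseline, and its test and arm sizes cannot be seen. Section 2.6.1 claims significance only for outcomes in general, and section 2.4.1 names pain on neuropathy questionnaires and electrophysiology. So nothing here shows the source to be misreported.

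A reader might also scale the 1.8 points down by the share of participants with diabetes or raised glucose, using the Introduction's figures. Those are upper limits from different groups; one set refers to the time before leprosy is diagnosed ("patients are statistically significantly more likely to have diabetes (up to 14.2%) or pre-diabetes (up to 50%), when compared to healthy controls"). The protocol also hypothesises direct neuroprotective effects that do not depend on diabetes. A calculated dilution would therefore be guesswork.

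Finally, a one-sided test would change the picture: with the pooled SD it needs 54 in total, so 60 would exceed 80%. Nothing in the article states a one-sided test.

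**Conclusion.** The sentence calling the estimate conservative is unsupported and should go. The planning effect is one small trial's observed difference, borderline on the printed figures, taken from an all-diabetic cohort and used without margin. With both printed SDs and two-sided alpha 0.05, 60 evaluable participants give about 73% power for that effect (69% to 78% across the two SDs), about 7 percentage points below the stated 80%. The difference detectable with 80% power is about 1.95 points.

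This rests on reading the printed alpha as 0.05, on a two-sided t-test, on equal arms, and on 30 per arm remaining after the planned loss. It would be tempting to describe 80% as a best case that weakens only if the effect is smaller in leprosy. That does not fit these figures, since 80% is missed even at the full 1.8 points. Nor do the documents rule out a larger effect in leprosy, though they give no evidence for one.

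**What to change.** In section 2.6.1:
- Delete the sentence calling the estimate conservative.
- Keep 70 enrolled. State that 1.8 points is the difference observed in one 34-person, all-diabetic trial, used as a proxy without margin for imprecision or for a different population.
- Replace the 80% power figure and the claim of adequate power with about 73% power for 1.8 points at 60 evaluable (two-sided 0.05, both SDs), and a detectable difference of about 1.95 points at 80% power.
- Show power at smaller differences, for example 58% at 1.5, 41% at 1.2 and 25% at 0.9 points.

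The cost is rewriting one paragraph and adding one line of figures. No participants, visits or measurements are added. The price is a less favourable stated power.
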